#### Item 20b

##### Additional analysis

Subgroup analysis may be conducted based on the clinical age group criteria and grams of alcohol consumed criteria. The imbalanced baseline characteristics will not be included in the primary analysis; however, we will conduct additional exploratory analysis where such characteristics will be included to assess the robustness of the primary analysis.

#### Item 20c

##### Subject population (S) for analysis

Common sensitivity analyses will be attempted to assess the robustness of the results to protocol deviations. For primary survival (efficacy) analysis, we will use intention to treat analysis, in such a way that all study subjects who are randomized, regardless of adherence to study medication, will be used in the analysis in the experimental arms to which they are originally allocated. As a supplementary analysis, we will perform a per-protocol analysis using patients who will achieve at least 80% compliance (without any major protocol violations) with experimental arms. Significance will be assessed using a two-sided alpha level of 0.05.

#### Analysis of missing data

It is important to document and investigate the reasons for loss to follow-up. We will examine the distribution of baseline characteristics between patients who completed the treatment with those who dropped out within each treatment group to identify the known factors associated with the poor treatment compliance.

We will use Rubin’s multiple-imputation method to deal with the missing data. Although the multiple-imputation method is developed based on the missing at random (MAR) assumption, this method can handle both missing completely at random (MCAR) and missing not at random (MNAR).

Another approach is a tipping point analysis, a multiple imputations technique under MNAR assumption and will be used to impute the missing data not at random. Under this analysis, a tipping point can be defined as the difference of means for continuous data and the difference of event numbers for binary data where the *p*-values get changed. This method does not require assessing the missing data mechanism and does not involve model uncertainty and assumptions.

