#### Statistical methods

The baseline patients’ characteristics mentioned in Annexure 2 including comorbid-conditions will be compared between the two treatment groups to demonstrate the actual study group balance and to ensure whether a proper randomization is established or not. We will measure central tendency and variability with means and standard deviations or medians and interquartile range for continuous characteristics and frequencies with percentages for categorical characteristics.

For primary outcome “survival at 3 months,” we will first use an unadjusted log-rank test of the Kaplan–Meier survival estimates for the two treatment arms at a two-sided alpha level of 0.05 with survival censored at 3 months. Further, a Cox proportional hazards regression model (with survival censored at 3 months) will be used to estimate the hazards ratio (HR) with 95% confidence interval (CI) associated with treatment arm (A) compared to the reference treatment (B). Parameters which are observed as unbalanced between the groups will be adjusted in the above model. We will also add any potential time-dependent covariates to the model, such as AST and ALT levels at months 1, 2, and 3 to estimate their predictive value for mortality.

Similar unadjusted log-rank test of the Kaplan–Meier survival estimates, and Cox proportional hazards regression model analysis will be planned for secondary outcome survival at 1 month. Other secondary outcomes measures such as change in mDF levels/MELD score, endotoxin levels, and cytokines levels between baseline and 4-week assessment will be assessed for normal distribution by graphical (Q–Q Plot) interpretation and numerical method (Kolmogorov–Smirnov test). A paired *t*-test will be used for all those outcomes which will follow approximately normal distribution and a sign-rank test will be used for skewed parameters. Proportionality assumption will be assessed for the considered ordinal outcome number of episodes of sepsis (pneumonia, SBP, cellulitis, and UTI). Partial proportional odds ratio regression will be used to assess the effect of treatment on the number of episodes of sepsis (pneumonia, SBP, cellulitis, UTI) over 4 weeks. A proportional partial odds model will be used if the treatment group variable will not meet the proportional odds assumption and will have different effects on different severity levels of sepsis.

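### The missing-data section wrongly credits standard multiple imputation with handling MNAR and calls the tipping-point analysis assumption-free, and its tipping point is not defined on the log-rank/Cox scale of the primary analysis

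*Protocol article*

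**What the plan says.** All references are to the protocol article.

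- **Analysis of missing data, multiple imputation.** The plan is: "We will use Rubin’s multiple-imputation method to deal with the missing data". The section notes that the method was developed under MAR, then adds that "this method can handle both missing completely at random (MCAR) and missing not at random (MNAR".
- **Analysis of missing data, tipping point.** The second method is introduced as follows: "Another approach is a tipping point analysis, a multiple imputations technique under MNAR assumption". Its scale is given: "a tipping point can be defined as the difference of means for continuous data and the difference of event numbers for binary data". The section closes on it with: "This method does not require assessing the missing data mechanism and does not involve model uncertainty and assumptions".
- **Statistical methods {20a}, primary outcome.** The primary test reads: "we will first use an unadjusted log-rank test of the Kaplan–Meier survival estimates for the two treatment arms at a two-sided alpha level of 0.05". The follow-up limit is given as "with survival censored at 3 months". The effect estimate comes next: "a Cox proportional hazards regression model (with survival censored at 3 months) will be used to estimate the hazards ratio (HR". It is to carry a 95% confidence interval.
- **Sample size determination {14}.** Survival of 22% vs 42% at 3 months, 79 per group, 10% dropouts, 174 in total.

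Neither analysis section says how a patient lost before day 90 enters the log-rank test. The censoring phrase describes the end of the 3-month window.

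**The concern.** There are two wrong statements and one mismatch.

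1. Multiple imputation from a MAR model does not become valid under MNAR. It needs an explicit departure, such as a delta adjustment or a pattern-mixture model, and the sentence attaches none. It credits the MAR-based method itself.
2. A tipping-point analysis works by imposing a graded series of MNAR assumptions on top of an imputation model. To say that it involves no assumptions is false, and it conflicts with the same paragraph's description of the method.
3. The stated tipping point compares means or event numbers. The primary test compares event times.

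At stake is what the trial report may claim. With these sentences in the plan, a report could say that MNAR was covered by multiple imputation, or that the tipping result holds whatever the missingness mechanism. It could also present a count-based tipping point as the tipping point of the log-rank result.

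**Working it through.** **Statements side by side.** The tipping-point method is said to operate under an MNAR assumption and also to involve no assumptions. Both cannot be true. The multiple-imputation sentence names MAR as the basis and then claims MNAR without adding any model. No detail in an unseen analysis plan would make either sentence correct.

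**The plan's own figure.** The sample size is not in dispute, and it reproduces on the log-rank scale:
- HR = ln(0.42)/ln(0.22) = 0.573.
- Freedman events = (1.960 + 0.842)² × [(1 + 0.573)/(1 − 0.573)]² = 106.5, so 107.
- Mean death probability = (0.78 + 0.58)/2 = 0.68, and 107/0.68 = 157.4, so 158, or 79 per group.
- 158 × 1.10 = 173.8, so 174.

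**Inputs for the illustration (assumed data).** 174/2 = 87 per arm. 10% of 87 is 8.7, taken as 9 lost per arm, leaving 78 observed. All 9 are assumed to have unknown vital status at day 90. Binary p-values are two-sided, from the pooled test without continuity correction: z = (p₁ − p₀)/√[p̄(1 − p̄)(2/n)].

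**A. Design rates.** 0.42 × 78 = 32.8, so 33 colostrum survivors. 0.22 × 78 = 17.2, so 17 placebo survivors. For 33/78 vs 17/78, z = 2.75 and p = 0.006. Now let all 9 lost colostrum patients die and k of the 9 lost placebo patients survive (33/87 vs (17 + k)/87):

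| k | 2 | 4 | 5 | 9 |
|---|---|---|---|---|
| p | 0.020 | 0.049 | 0.073 | 0.26 |

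Over the full 10 × 10 grid of lost survivors per arm, p never exceeds 0.05 with fewer than 5 lost placebo survivors. If 1, 2, 3, 4 or 5 lost colostrum patients survive, the smallest number of lost placebo survivors that tips is 5, 6, 7, 8 or 9 (p = 0.052, 0.054, 0.056, 0.058, 0.059).

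**B. A borderline result, chosen to lie near 0.05.** 29/78 vs 17/78 gives p = 0.035. Imputing the lost at the observed rates gives 9 × 29/78 = 3.3, so 3 colostrum survivors, and 9 × 17/78 = 2.0, so 2 placebo survivors. That is 32/87 vs 19/87: p̄ = 51/174 = 0.293, z = 0.149/0.0690 = 2.17, p = 0.030. Keep 19 placebo survivors and lower the lost colostrum survivors to 2, 1 or 0 (31, 30 or 29 of 87): p = 0.044, 0.064, 0.090. Two fewer survivors than the observed rate implies, or one fewer than equal numbers in both arms, crosses 0.05.

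**C. Does the count fix the log-rank result?** Take the design-rate data with exponential death times: 61 placebo and 45 colostrum deaths among 78 per arm. With the 9 lost per arm censored at day 30, log-rank p = 0.004. Now impute 0 of 9 colostrum and 5 of 9 placebo survivors, for which the binary p is 0.073, and vary only the day of the imputed deaths:

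| Imputed deaths, colostrum / placebo | Log-rank p |
|---|---|
| day 89 / day 31 | 0.009 |
| day 60 / day 60 | 0.030 |
| day 31 / day 89 | 0.092 |

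The same counts fall on either side of 0.05 on the primary test.

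**The case against.** A reader might infer that the primary result gets no MNAR check at all, or that its censoring assumption is never tested. The documents do not support that. Deaths by day 90 are binary event numbers, the primary outcome is worded as survival at 3 months, and the sample-size section describes a fixed-time comparison. The stated rule can therefore be applied to the primary outcome, and its wording does not rule out other forms. What remains is narrower: a count-based tipping point is not the tipping point of the log-rank test.

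Nor does the plan say that lost patients are censored and that imputation stays out of the primary analysis. Censoring at loss is the usual reading, but the text fixes only the 3-month limit.

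It is also tempting to say that the trial result hangs on two or three patients. That is true only near the threshold (case B). At the design effect it takes the lopsided losses in case A.

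There is mitigation too. The section on study drug discontinuation provides for telephone contact with patients who stop, including those who refuse a final visit, and lists death among the items to record. Data management {18 b} keeps outcome data for patients who discontinue. The 10% dropout allowance therefore need not mean 10% with unknown vital status. Against this, the same telephone list includes worsening and treatment at another hospital, so loss related to prognosis is foreseeable.

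Finally, imputation covariates and shift sizes may properly sit in an analysis plan that is not shown, and their absence is no part of this point.

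**Conclusion.** The point holds in this form. Two sentences on missing data are wrong as written, and one of them contradicts its own paragraph. The tipping point is defined on scales that do not carry over to the log-rank/Cox primary analysis. What is affected is the robustness that the trial may claim. The primary test, alpha and sample size stand.

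The sizes are illustrations, not predictions. They assume 9 patients per arm with unknown vital status and, for the log-rank figures, exponential death times with imputed deaths placed on chosen days. On that basis a borderline result can turn on one or two lost patients. A result at the design rates tips, with every lost colostrum patient dead, only from 5 of 9 lost placebo survivors upward. The change should be made before unblinding.

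**What to change.** 1. Delete both claims. State that standard multiple imputation is valid under MCAR and MAR only, and that the tipping-point analysis imposes a graded series of MNAR assumptions.
2. State that the primary log-rank/Cox analysis censors patients lost before day 90 at the date last known alive, and that it assumes non-informative censoring.
3. Define the tipping analysis on the primary test: impute event times after censoring, raise the post-censoring hazard in the colostrum arm stepwise, repeat the log-rank test, and report the multiplier at which p first exceeds 0.05.
4. Keep the day-90 grid of deaths among lost patients per arm as a supplement, labelled as a binary analysis.

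The cost is a few sentences and a little programming. No new data, patients or alpha are needed. Step sizes and imputation covariates can go in the statistical analysis plan.

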#### Interim analyses

No formal interim analysis is planned for this trial.

## Methods: monitoring

### Composition of the data monitoring committee, its role and reporting structure

#### Data will be monitored by the Principal Investigator of each site {21a}

##### Monitoring frequency and agenda

Monitoring will be conducted at 4, 7, 21, 28, 45, 60, 75, and 90 days and relevant information will be shared by the Principal Investigator to DMEC. During each visit, Principal Investigator will discuss with DMEC all relevant issues pertaining to the trial, validate the CRFs with the source data, and identify and modify in case of any discrepancies or errors.

##### Source data verification

The source data verification and review of records is necessary to minimize any errors in transcribing data onto the CRFs. The monitor (PI) will validate the CRF entries with the source data and subjects’ records.

##### Data clarification / rectification

Data will be entered into the CRF by site personnel. Post data entry, source data verification will be completed by Study monitor (PI). If any query requires clarification from site, data management personnel will answer the query. If the response for raised query is satisfactory, then data management personnel will close the query or if response for raised query is not satisfactory then data management personnel will collect all query related data related to site to rectify any error that may have occurred.

##### Close-out meeting / site closure

At this visit, left over trial medication(s) and trial related materials will be collected. An accounting will be done of all materials supplied to the site, as well as all patients screened and enrolled.

### Description of any interim analyses and stopping guidelines, including who will have access to these interim results and make the final decision to terminate the trial {21b}

There will be no interim analysis.

#### Study drug discontinuation / stopping guidelines

After the patient has been enrolled into the study, his/her treatment will be discontinued by the Principal Investigator if one or more of the following pertain(s):Occurrence of adverse effects of bovine colostrum (Group A) and pasteurized milk powder (Group B): allergy or lactose intoleranceTreatment with prohibited concomitant medications, for example corticosteroids.

Patients who discontinue the study before completion of it will be scheduled for an end of study visit as soon as possible, at which time all of the assessments listed for the final visit will be performed.

At a minimum, all patients who discontinue the study, including those who refuse to return for a final visit will be contacted telephonically for the final visit clinical assessment:Improvement / worsening / death / started taking treatment from another hospitalSafety evaluations during the 30 days following the last dose of drug administration.

### {22} Harms

Plans for collecting, assessing, reporting, and managing solicited and spontaneously reported adverse events and other unintended effects of trial interventions or trial conduct.

#### Monitoring for adverse events

A treatment-emergent adverse event (AE) will be defined as an AE that begins or that worsens in severity after at least one dose of study drug has been administered. Any adverse event (AE) occurring during the study will be documented in the subject’s case report form (CRF) specifying the time of onset, the duration, the severity, and the relationship to the test medication.

Grades of Severity of the AE as per the Common Terminology Criteria for Adverse Events (CTCAE) v 5.0:Grade 1 Mild AEGrade 2 Moderate AEGrade 3 Severe AEGrade 4 Life-threatening or disabling AEGrade 5 Death related to AE

### Auditing {23}

Frequency and procedures for auditing trial conduct, if any, and whether the process will be independent from investigators.

This clinical trial will be audited by the Institutional Ethical Committee (IEC) to evaluate trial conduct and compliance with the protocol, standard operating procedure, and International Conference on Harmonization Good Clinical Practice (ICH-GCP) guidelines. The PI and his team will supply all the information regarding the trial conduct to the IEC. The frequency of the audit will be at 4, 7, 21, 28, 45, 60, 75, and 90 days of the trial.

## Ethics and dissemination

### {24} Plans for seeking research ethics committee/institutional review board (REC/IRB) approval

The study protocol, patient information sheet, and informed consent form (the latter two were created in three languages—Punjabi, Hindi, English) (Annexure No. 3) were submitted to the IEC of each site for approval.

Similarly, at all other trial sites, the respective IEC’s will give approval following which the study will be initiated at the respective sites.

### {25} Plans for communicating important protocol modifications (e.g., changes to eligibility criteria, outcomes, analyses) to relevant parties (e.g., every trial site Principal Investigator, IEC, trial participant, trial registry, journal, regulator)

Any modification in the research protocol final version or Statistical Analysis Plan will be submitted to all the different trial site Principal Investigators and their IECs. These changes will be modified on the ClinicalTrials.gov site.

### 26 a. Who will obtain informed consent or assent from potential trial participants or authorized surrogates, and how (see Item 32)

Informed Consent is documented by means of a written, signed, and dated informed consent form (in the language the patient reads and or writes: Punjabi, Hindi, English). The trial patients shall voluntarily confirm his / her willingness to participate in this trial, after having been informed of all aspects of the trial that are relevant to the subject’s decision to participate. In case of the patient’s inability to give the consent because of hepatic encephalopathy, *a legally acceptable representative*, usually an immediate relative, will give consent, on behalf of a prospective patient, to the subject’s participation in the clinical trial. If the patient / relative cannot read or write, then the PI will explain in a vernacular language all aspects of the trial including the risks and benefits of a medical intervention, which in this study is bovine colostrum or milk and obtain the consent easily as most subjects are familiar with these interventions (bovine colostrum or milk).

### Who will take informed consent?

The consent of the patients will be taken by the patient’s treating physician—Principal Investigator (PI)—after explaining the benefits and risks of participating in the study. The patient will be encouraged to ask questions regarding the study. They will be given a patient information sheet (PIS) and will be given 24 h to consider the study (or less if the patient feels that he / she has decided to participate in the study) and whether to participate, prior to giving their informed consent. Patients will be given a copy of the signed informed consent form (ICF).

Potential patients for the trial who present with hepatic encephalopathy may be unable to consent for themselves but are not excluded from the trial. An informed consent was taken from the nearest relative / legal representative of the patient for enrolment in the trial, until the patient recovered his mental faculty, at which point the patient was informed about the trial and asked to decide whether or not they wanted to continue in the study.

### Additional consent provisions for collection and use of participant data and biological specimens

Informed consent forms will include the option to consent for the collection, and use of, participant data and biological specimens in ancillary studies. These include analyses of serum biomarkers of disease.

### {26b}. Additional consent provisions for collection and use of participant data and biological specimens in ancillary studies, if applicable

NA

### {27}. How personal information about potential and enrolled participants will be collected, shared, and maintained in order to protect confidentiality before, during, and after the trial

It is the duty of physicians who are involved in medical research to protect the life, health, dignity, integrity, privacy, and confidentiality of personal information of research subjects.

*Every precaution will be taken to maintain the confidentiality of their personal information.* Subjects must be identified only by their assigned identification number and initials on all CRFs and other records and documents.

### {29}. Statement of who will have access to the final trial dataset, and disclosure of contractual agreements that limit such access for investigators

All Principal Investigators and site study personnel will have access to final trial dataset. There are no contractual agreements.

### {30}. Provisions, if any, for ancillary and post-trial care, and for compensation to those who suffer harm from trial participation

The patients will be given standard medical treatment after termination of the study. No compensation needs to be given as the experimental product is a food supplement.

## Dissemination policy

### {31} a Plans for investigators to communicate trial results to participants, healthcare professionals, the public, and other relevant groups (e.g., via publication, reporting in results databases, or other data sharing arrangements), including any publication restrictions

We, as Principal Investigators conducting this clinical trial, have registered this clinical trial is registered at ClinicalTrials.gov—ClinicalTrials.gov Identifier: NCT02473. The summary of results information will be submitted to ClinicalTrials.gov for public posting. Disseminating this information will help to advance the translation of research results into knowledge, products, and procedures that improve human health in patients with SAH. Results information from this trial will be submitted not later than 1 year after the trial’s primary completion date.

The completed study shall be submitted for publication in an appropriate medical journal. Negative and inconclusive as well as positive results will be published. Institutional affiliations will be declared in the publication.

### {31b}. Authorship eligibility guidelines and any intended use of professional writers

Authors will be selected based on the authorship criteria mentioned by International committee of medical journal editors. The corresponding author takes primary responsibility for communication with the journal during the manuscript submission, peer review, and publication process. This author ensures that all the journal’s administrative requirements, such as providing details of authorship, ethics committee approval, clinical trial registration documentation, and disclosures of relationships are reported

